### Exclusion criteria

(1) Unstable condition or recurrence of stroke during the treatment period; (2) Severe bleeding tendency, or concurrent failure of vital organs such as the heart, liver, or kidneys; (3) Insomnia caused by other definite etiologies; (4) Comorbid severe mental illness; (5) Currently participating in other clinical trials; (6) Contraindications to MRI; (7) Hemorrhagic stroke patients; (8) History of ear infection or prior vagus nerve surgery.

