### Inclusion criteria

(1) Confirmed by MRI and meeting the diagnostic criteria for ischemic cerebrovascular disease; (2) Aged between 40 and 80 years, regardless of gender; (3) Insomnia first occurring more than 2 weeks after acute stroke, with no prior history of insomnia; (4) Pittsburgh Sleep Quality Index (PSQI) score > 7; (5) Conscious and able to cooperate with all scale assessments; (6) Voluntary participation in the study, signing the informed consent form, and committing not to participate in other clinical studies during the treatment period.

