### Withdrawal criteria

(1) Severe adverse reactions or allergic reactions; (2) Significant disease progression.

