### Blinding

To ensure methodological rigor, this trial adopts a single-blind design. Participants will be blinded to group allocation and treated in separate rooms to minimize communication between groups. To assess the effectiveness of the blinding, participants will be asked to guess their group assignment (taVNS group or sham-taVNS group) after the intervention. Due to the specific nature of the taVNS intervention, the therapists cannot be blinded. In contrast, both the outcome assessors and the statistical analysts will remain blinded to the group assignments throughout the study.

Eligible participants will be randomly assigned to the taVNS group or sham-taVNS group in a 1:1 ratio using a computer-generated random sequence. Allocation concealment will be maintained using sequentially numbered, opaque, sealed envelopes prepared by an independent researcher who is not involved in recruitment, intervention, outcome assessment, or data analysis.

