### Basic treatment

During the 4-week intervention period, all participants will receive standard basic treatment, including conventional post-stroke medication and rehabilitation training. Medication will be administered in accordance with the *Chinese Guidelines for the Diagnosis and Treatment of Acute Ischemic Stroke 2023* (35). Rehabilitation training will include functional training, routine medical care, and other standard rehabilitation procedures.

To avoid potential confounding effects on sleep outcomes and multimodal MRI indicators, sedative-hypnotic drugs will not be routinely prescribed during the study period. Estazolam will be permitted only as rescue medication when participants experience severe or intolerable insomnia, such as inability to sleep for two consecutive nights or when clinically judged necessary by the investigator. The recommended rescue dose will be estazolam 1 mg orally before bedtime. The use of rescue medication, including dosage, frequency, and timing, will be recorded in detail throughout the study. Participants will be instructed to avoid taking estazolam within 48 hours before MRI scanning and clinical assessments whenever clinically feasible.

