### Patient safety

Any Adverse Events (AEs) or Serious Adverse Events (SAEs) occurring during the intervention period, regardless of whether the investigator considers them to be related to the taVNS intervention, will be accurately and thoroughly documented in the case report form to allow for a rigorous assessment of their relevance. For common mild adverse events associated with taVNS, such as erythema of the auricular region, tingling or burning sensations, contact dermatitis, and occasional dizziness, the investigator will immediately implement symptomatic management, such as suspending stimulation, adjusting parameters, or providing local skin care. Given that the study participants are post-stroke insomnia patients with underlying cardiovascular and cerebrovascular risk factors, if serious adverse events such as stroke recurrence, severe heart failure, or acute organ injury occur, the investigator will immediately discontinue the intervention and promptly transport the patient to the emergency department or a neurology specialty unit for emergency treatment; any related medical expenses incurred will be borne by the research team. Furthermore, any serious adverse event must be urgently reported to the hospital’s Institutional Review Board (IRB) and relevant administrative departments within 24 hours of becoming known, in strict accordance with standardized procedures.

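### Exclusion criterion (1) names stroke recurrence on treatment, which can only happen after randomisation, and two other sections classify the same event differently

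*Protocol article*

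**What the plan says.** Exclusion criteria, item (1), reads "Unstable condition or recurrence of stroke during the treatment period". The phrase for the period also appears in Inclusion criteria, item (6), where participants sign up to "committing not to participate in other clinical studies during the treatment period". There it plainly means this trial's own treatment. Basic treatment gives its length: "During the 4-week intervention period, all participants will receive standard basic treatment".

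The Blinding section sets the order of events: "Eligible participants will be randomly assigned to the taVNS group or sham-taVNS group in a 1:1 ratio". Eligibility therefore comes before allocation, and treatment comes after it.

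Two other sections deal with the same kind of event. Withdrawal criteria, item (2), is "Significant disease progression", without saying what the patient is withdrawn from. Patient safety provides that "if serious adverse events such as stroke recurrence, severe heart failure, or acute organ injury occur", "the investigator will immediately discontinue the intervention" and the patient is sent for emergency care. It also requires every adverse event in the intervention period to be documented, and serious ones to be reported within 24 hours.

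**The concern.** An eligibility criterion has to be decidable before allocation. At least the recurrence half of item (1) is not. A patient who has a second stroke in week 3 was eligible when randomised and, read literally, meets an exclusion criterion afterwards.

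The status of that patient matters. Someone excluded as ineligible, someone withdrawn, and a participant who stops stimulation but stays in the trial differ in what follow-up is collected and in whether they count in the comparison. The article supports all three labels for one event.

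The event is also prognostic. The Introduction describes post-stroke insomnia as an independent risk factor for stroke recurrence, and a new stroke would plausibly worsen the NIHSS and ADL scores. The patients affected would tend to be those doing badly. The instability half of the criterion is not defined, and the therapists know the allocation, so uneven application between arms is possible. If such patients were dropped, the arm that lost more of them would look better than it is.

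**Working it through.** **Sequence.** Eligibility is settled, then participants are randomised, then the 4-week treatment period runs. Recurrence during that period falls in the third step, while the criterion belongs to the first. Instability could have been meant as a state at screening; recurrence during treatment cannot be read that way.

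**The same event in three sections.**

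| Section | Treatment of on-treatment recurrence |
|---|---|
| Exclusion criteria (1) | patient is ineligible |
| Withdrawal criteria (2) | arguably a withdrawal, if it counts as significant progression |
| Patient safety | serious adverse event; intervention discontinued |

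**Figures.** The article gives no rate of recurrence or instability, so there is no figure of its own to reproduce. The only inputs it supplies are 24 per arm, 48 in total, and a two-sided 5% level for the clinical data. The rest is assumption.

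*How often the criterion might be met.* With an assumed 4-week event rate p, the expected number is 48p and the chance of at least one is 1 − (1 − p)^48.

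| Assumed p | Expected among 48 | Chance of at least one |
|---|---|---|
| 1% | 0.5 | 38% |
| 2% | 1.0 | 62% |
| 5% | 2.4 | 92% |
| 10% | 4.8 | 99% |

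*How far a scale comparison could shift.* Assume no true effect, and that excluded patients are worse than retained ones by g SD. If a proportion e of an arm is excluded, the retained mean rises by g × e. The bias in the between-group difference is therefore g × (e1 − e0). The standard error, in SD units, is √[1/(24(1 − e1)) + 1/(24(1 − e0))], and the error rate uses a normal approximation.

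| Excluded, arm 1 vs arm 0 | Bias, g = 1.0 | Bias, g = 1.5 | Two-sided error rate |
|---|---|---|---|
| 5% vs 5% | 0 | 0 | 5.0% |
| 2/24 vs 0/24 | 0.083 SD | 0.125 SD | 5.9% to 7.1% |
| 10% vs 5% | 0.05 SD | 0.075 SD | 5.3% to 5.7% |
| 20% vs 5% | 0.15 SD | 0.225 SD | 7.7% to 11.2% |

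Example: 20% vs 5% with g = 1.5 gives 1.5 × (0.20 − 0.05) = 0.225 SD. The standard error is √(1/19.2 + 1/22.8) = 0.310, and 0.225/0.310 = 0.73 standard errors, which raises the error rate from 5% to 11.2%.

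The zero in the first row depends on g being the same in both arms. Equal numbers of different kinds of patient could still bias the comparison.

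**The case against.** The strongest reply is that nothing in the article says these patients leave the analysis. Item (1) lists a criterion, the withdrawal list does not mention analysis, and Patient safety only stops the intervention. The sample size section does allow for exclusions, but that may refer to scans rejected for head motion. The statistical analysis plan is not shown and may keep everyone as randomised. This stands: a reader might infer that randomised patients will be removed and the comparison will cease to be as randomised, but the text supports only that they could be. It does not rescue the criterion, because a plan that retained these patients would sit uneasily with a rule calling them ineligible.

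A reader might also infer that recurrences would vanish from the safety results and make an arm look safer. The article does not support this. Patient safety requires every adverse event to be documented whether or not it is thought related, and it names stroke recurrence as serious. Data management requires progress reports covering adverse events, withdrawals and deviations.

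It is tempting, too, to express the bias as a share of the effect detectable with 24 per arm. That benchmark comes from a single unadjusted t-test. The primary outcomes are voxel-wise or vertex-wise maps with cluster correction, so it does not describe them.

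Finally, a patient with a new infarct may have no usable week-4 scan, so rewording the criterion cannot fully restore the primary imaging comparison. This stands as well, and it limits what the fix can achieve.

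**Conclusion.** The point holds as a wording defect with a conditional risk of bias. An event that, at least for recurrence, can only occur after randomisation is placed among the eligibility criteria, and the sections on exclusion, withdrawal and safety do not agree on its status. Bias follows only if affected patients are dropped and if the exclusions differ between arms in number or type. It would fall mainly on the clinical scales.

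Its size cannot be obtained from the document. Under the assumed deficit of 1 to 1.5 SD it runs from none with equal exclusion of similar patients, through 0.05 to 0.08 SD at 10% versus 5%, to 0.15 to 0.23 SD at 20% versus 5%. The last case requires very uneven exclusion. The amendment is worth making because the ambiguity is plain and the correction is cheap, not because a large bias has been shown.

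**What to change.** - Restrict item (1) to a condition that is judged before randomisation.
- Reconcile Exclusion criteria, Withdrawal criteria and Patient safety so that recurrence or instability on treatment is handled only as an adverse event or discontinuation of the intervention. No change to when the intervention is stopped is proposed.
- Keep these patients in their randomised arm for the scale analyses, collecting the week-2 and week-4 scales where possible.
- Keep them in the imaging analysis where a usable week-4 scan exists, and report by arm how many have none.

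The cost is a minor amendment to one criterion and a sentence or two on how these patients are handled. Enrolment stays at 48. The downside is somewhat more variable outcomes, with some post-treatment scans missing or altered by a new lesion.

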### Withdrawal criteria

(1) Severe adverse reactions or allergic reactions; (2) Significant disease progression.

### Sample size calculation

Currently, no precise method exists for calculating the sample size for acupuncture neuroimaging trials. Based on international reviews, a minimum of 12 cases per group is recommended (29, 30). To account for potential data loss and exclusions, this trial will enroll 24 subjects per group, totaling 48 participants.

### Blinding

To ensure methodological rigor, this trial adopts a single-blind design. Participants will be blinded to group allocation and treated in separate rooms to minimize communication between groups. To assess the effectiveness of the blinding, participants will be asked to guess their group assignment (taVNS group or sham-taVNS group) after the intervention. Due to the specific nature of the taVNS intervention, the therapists cannot be blinded. In contrast, both the outcome assessors and the statistical analysts will remain blinded to the group assignments throughout the study.

Eligible participants will be randomly assigned to the taVNS group or sham-taVNS group in a 1:1 ratio using a computer-generated random sequence. Allocation concealment will be maintained using sequentially numbered, opaque, sealed envelopes prepared by an independent researcher who is not involved in recruitment, intervention, outcome assessment, or data analysis.

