### Interventions

In the taVNS group, a taVNS device will be used (Hwato, SDZ-IIB, Suzhou, China) to stimulate the auricular branch of the vagus nerve distribution area located posterior and inferior to the external auditory meatus, with clear anatomical localization. The stimulation parameters will be as follows (31, 32): (1) dense-sparse waves with a pulse frequency of 4/20 Hz; (2) current intensity of 3–14 mA, individually adjusted according to the patient’s tolerance; (3) stimulation time of 30 min per session. Patients will be placed in a comfortable position. The treatment will be administered once daily, five days per week, for a total of four weeks. These parameters were chosen on the basis of our team’s previous taVNS trials in primary insomnia and depression, in which the same dense-disperse 4/20 Hz waveform and 30-minute daily session produced clinical benefit with good safety and tolerability (15, 31, 32). The auricular branch of the vagus nerve distribution was selected as the stimulation target because this region is densely innervated by vagal afferent fibers, enabling direct, non-invasive activation of the vagal pathway. The current intensity will be individually titrated within the 3–14 mA range to the highest level that evokes a distinct but non-painful tingling sensation, so as to ensure adequate afferent activation while maintaining tolerability and minimizing the risk of adverse effects (10). The 4-week course was set to match the intervention duration shown to be effective in our prior insomnia studies and to align with the typical timescale of post-stroke neuroplastic change.

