In the sham-taVNS group, the same therapeutic device will be used, but the stimulation site will be the superior scaphoid fossa at the midpoint of the external auricular margin, an area not innervated by the vagus nerve (**Figure 2**). The selection of this site as the sham target is supported by authoritative anatomical evidence. In the classic cadaveric dissection of the human auricle, the auricular branch of the vagus nerve was found to innervate the cymba conchae (100%), the cavity of concha, and the tragus, whereas the scapha and scaphoid fossa receive their cutaneous innervation from the great auricular and auriculotemporal nerves rather than the vagus nerve (33). Accordingly, the superior scaphoid fossa lies outside the vagal innervation territory and is not expected to activate central vagal afferent pathways. Consistent with this anatomy, the scaphoid fossa has been adopted as a non-vagal sham site in previous double-blind, sham-controlled taVNS trials, in which stimulation of this region produced comparable tactile sensation without engaging the vagal pathway (34). The stimulation parameters and treatment course will be the same as those in the treatment group.

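### Visible skin reactions sit at an arm-specific ear site and could unblind assessors who see the ear at the Week 2 and Week 4 ratings

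*Protocol article*

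**What the plan says.** All of the following is in the Methods of the protocol article.

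- **Blinding.** Therapists cannot be blinded. For the others the commitment is unqualified: "both the outcome assessors and the statistical analysts will remain blinded to the group assignments throughout the study". The one check described concerns participants: "participants will be asked to guess their group assignment (taVNS group or sham-taVNS group) after the intervention".
- **Interventions, active arm.** Stimulation is applied to the vagal area "located posterior and inferior to the external auditory meatus", once daily, five days a week, for four weeks.
- **Interventions, sham arm.** The same device is used, but "the stimulation site will be the superior scaphoid fossa at the midpoint of the external auricular margin". On settings, "The stimulation parameters and treatment course will be the same as those in the treatment group".
- **Patient safety.** The common mild events are "erythema of the auricular region, tingling or burning sensations, contact dermatitis, and occasional dizziness". The investigator manages them. All adverse events "will be accurately and thoroughly documented in the case report form".
- **Secondary outcomes.** PSQI, NIHSS, ADL, HAMD-17 and HAMA-14 are assessed at baseline, Week 2 and Week 4. PSQI is the principal secondary endpoint; the other four are supportive.

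**The concern.** The stated difference between the arms is the place on the outer ear where the current is applied. If the skin reacts, the position of the redness or dermatitis shows which arm the participant is in. Week 2 falls in the middle of the treatment course and Week 4 at its end, so the ratings take place when a recent reaction is most likely to be visible.

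Because therapists know the allocation, blinded assessment is the main protection for scales that depend on a rater's judgement. A rater who has inferred the arm may score in line with expectation, most plausibly in favour of taVNS. That would affect the between-arm comparisons of those scales. It would also affect the planned correlations of scale changes with imaging changes, which include the Discussion's hypothesis linking HAMD and HAMA reductions to regional brain changes. The described check asks participants only, so it would not detect this.

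**Working it through.** The plan gives no figure on this point, so there is none to reproduce. The check sets the sections side by side and adds one illustration of scale.

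**Which events can reveal the arm.** Four kinds of event are named. Erythema and contact dermatitis leave a visible mark at the site. Tingling or burning and dizziness are symptoms and show an observer nothing about the site. Only the first two matter here.

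**Can they occur in both arms?** Yes. Settings and course are the same, so a reaction is possible at either site.

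**What must happen for an assessor to be unblinded.** A mark must be present at the rating visit, the assessor must see it, and the assessor must know which site is active. The article does not establish the last two. Nor does it make them unlikely: the auricle is normally in view during a face-to-face rating, this is a single-centre trial, and both sites are described and illustrated in the article.

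**Which outcomes are exposed.**

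| Outcome | Role in the plan | Exposure by this route |
|---|---|---|
| MRI indicators | Primary | Largely none: derived by software pipelines, analysts stated to be blinded |
| PSQI | Principal secondary | Little: described as reflecting subjective sleep quality |
| NIHSS, ADL, HAMD-17, HAMA-14 | Supportive secondary | Main exposure |
| Correlations of these scales with imaging | Planned analysis | Through the scale scores |

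**Scale, as an illustration.** The inputs are N = 48 (Sample size calculation) and a visible-reaction rate r. The documents give no r, so the range below is an assumption.

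Expected number with a visible reaction = 48 × r. Probability of at least one = 1 − (1 − r)^48.

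| r (assumed) | Expected number of 48 | P(at least one) |
|---|---|---|
| 2% | 0.96 | 0.62 |
| 5% | 2.4 | 0.92 |
| 10% | 4.8 | 0.99 |
| 20% | 9.6 | >0.99 |
| 30% | 14.4 | >0.99 |

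At each r, these are upper limits on unblinding by this route, because the further conditions above must also hold.

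**The case against.** **Practical masking steps belong in the full protocol.** Ear covering, form layout and access rights are details that a journal article commonly leaves out, and nothing in the article contradicts the blinding commitment. This stands in part: the point is not an internal contradiction, and silence does not prove that no safeguard exists. What remains is a design consequence of the text. The chosen sham site, the named skin reactions and the rating schedule together make a foreseeable route to unblinding, and a simple arm-symmetric step would close it.

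**Safety records do not unblind anyone.** A reader might infer that thorough documentation in the case report form carries the reaction site to assessors and analysts. The article does not support this. It does not say that the position on the ear is recorded, that assessors see adverse event pages, or that analysts receive such a variable. It gives management of these events to the investigator and does not equate that role with the outcome assessor. This objection stands, and the point rests on direct sight of the ear.

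**The bias can be quantified.** A reader might assume a 2-point HAMD-17 shift in marked participants at reaction rates of 10–30%. That gives 2 × 0.10 = 0.2 to 2 × 0.30 = 0.6 points per arm, or 0.4 to 1.2 points between arms if the shifts run in opposite directions. Neither the shift nor the rate is in the documents. The sum also assumes that every mark is seen, decoded and acted on in both arms. With the same shift and a 2% rate it is 2 × 0.02 × 2 = 0.08 points. No such figure should be read as an estimate of the bias.

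**Asking assessors to guess would not settle it.** A guess made after rating is confounded with perceived improvement. This stands, so such a question is optional.

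**Conclusion.** The point holds as a limited risk. Erythema or contact dermatitis would appear at an arm-specific site and could unblind an assessor who sees the ear at Week 2 or Week 4, despite the promise of blinding throughout. The consequence is confined mainly to NIHSS, ADL, HAMD-17 and HAMA-14 and their correlations with imaging. It does not threaten the MRI primary outcome to any material degree, and it gives no ground for saying that analysts would be unblinded.

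The size of any bias cannot be estimated from the documents. The conclusion assumes that some visible reactions occur, that ears are uncovered at ratings, and that some assessors can tell which site is active. The first is supported by the article's own list of common events. The other two are plausible but not stated.

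**What to change.** - Cover both ears in the same way in every participant, in both arms, at the Week 2 and Week 4 scale assessments.
- Have existing staff who do not rate outcomes inspect the ears and record the site of any local reaction. Withhold site details from raters and analysts until database lock.
- State both steps in the Blinding section, beside the commitment that they protect.
- Optionally, ask assessors to guess the allocation, and read the answers with the caution given above.

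The cost is a cap or dressing and slightly more form handling. No extra visits or staff are needed, and the management of adverse events does not change.
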